#### Mixed methods assessments

To assess acceptability, appropriateness, and feasibility, we will conduct mixed methods assessments at multiple time points. Pre-implementation, we will perform baseline assessments at each facility and administer readiness assessment surveys to small groups of key stakeholders, including representatives from MoH district health management teams and community leaders. We will also conduct the first round of in-depth interviews (IDIs) with facility managers and coordinators and focus group discussions (FGDs) with clinic providers and HSAs. Each IDI/FGD participant will complete a survey before the discussion in which they rank the acceptability, appropriateness, and feasibility of the interventions.

During implementation, we will conduct three rounds of implementation evaluations at early (0–3 months after implementation), midline (5–7 months), and final (13–15 months) time points. These mixed methods assessments will include manager IDIs, provider FGDs, acceptability-appropriateness-feasibility surveys, Client Exit Surveys, and Workload Assessment Surveys. We will conduct client IDIs in months 7–13 after implementation. Throughout implementation, the study team will use an observation checklist to determine how closely facility staff is adhering to our interventions. All surveys will be administered by interviewers.

At the end of the pre-implementation assessment and each round of mixed methods assessments, the study team will convene stakeholders meetings at district and facility levels to validate the findings and seek explanation from the stakeholders on the potential reasons for our successes or failures. Any recommendations from the stakeholders about how to modify study interventions will be documented.

#### Cost and budget impact

Cost and budget information will be obtained from multiple sources, including the time-and-motion evaluations (conducted pre- and post-implementation), the Client Exit Survey, the Workload Assessment Tool, project reports, and account expenditure reports. Key activities that will be costed include provider wages and time, health worker training and briefings, community sensitization, development of project materials, and patient costs.

### Analysis plan

#### Endline Household Survey

Key outcomes from the Endline Household Survey include (1) the proportion of eligible women who have received CCS during the 18 months of study implementation, (2) the proportion of treatment-eligible women who received thermal ablation during the study period, and (3) the proportion of women aged 15–50 years who are using a modern FP method. These proportions will be calculated using descriptive statistics. Differences between the clinic-only and clinic-and-community models will be assessed via logistic regression, adjusted for district, facility size, and facility type. The regression model will account for health facility clustering, and analyses will be adjusted for the small number of clusters [28, 29].

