**Methods:**

We designed a cluster randomized feasibility trial to determine the effectiveness, acceptability, appropriateness, feasibility, and budget impact of two models for integrating a HPV-based CCSPT program into family planning (FP) services in Malawi: model 1 involves only clinic-based self-sampled HPV testing, whereas model 2 includes both clinic-based and community-based self-sampled HPV testing. Our algorithm involves self-collection of samples for HPV GeneXpert® testing, visual inspection with acetic acid for HPV-positive women to determine ablative treatment eligibility, and same-day thermal ablation for treatment-eligible women. Interventions will be implemented at 14 selected facilities. Our primary outcome will be the uptake of cervical cancer screening and family planning services during the 18 months of implementation, which will be measured through an Endline Household Survey. We will also conduct mixed methods assessments to understand the acceptability, appropriateness, and feasibility of the interventions, and a cost analysis to assess budget impact.

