Service utilization data	De-identified information about CCSPT and FP services will be collected from clinic, HSA, and lab registers on a monthly basis.	Providers routinely record visit information in registers; research team members collect data	N/A (difficult to estimate projected number of clients for each register type)
Time and motion study	Research assistants will continuously observe providers, e.g., nurses and HSAs record the time spent on health care activities such as CCSPT and FP including non-health care activities	Providers, nurses, clinicians, HSAs, and lab staff	At least 1 staff member per facility from each category (e.g. provider, HSA, lab staff).
Client Exit Survey	This survey asks clients about the money and time expended accessing CCSPT and FP services at the clinics. It also includes the EQ-5D-3L survey to assess health-related quality-of-life for the cost impact analyses.	Facility clients	Up to 2370 participants (790 participants each at 3 time points, with the number of participants interviewed per facility proportional to the number of FP clients at that facility)

Throughout the implementation period, we will conduct weekly clinical supportive supervision visits and mentor the health facility providers, ensure appropriate logistical support, and assess providers’ fidelity to our protocols. Of note, while our study is ongoing, we will not restrict concomitant care or interventions at the study sites. Specifically, facilities are permitted to continue offering VIA and cryotherapy.

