### Sample size calculations

Sample size calculations were based on the ability to detect a difference in service uptake through the Endline Household Survey. As noted earlier, only 26.5% of Malawian women had been screened at least once in their lifetime as of 2015 with use of VIA for primary screening [3], which is much lower than the targeted rate of 80% set at the onset of Malawi’s Cervical Cancer Control Program in 2004 [16]. We estimated that with the introduction of HPV self-sampling in our clinic-only arm, at least 40–50% of eligible women in our facility catchment areas will be screened during our 18 months of implementation. We then estimated that with the addition of HPV self-sampling in the community to reach rural women, we would be able to approach Malawi’s targeted rate of 80% of eligible women screened in our clinic + community arm. Based on data obtained from potential facilities in Lilongwe and Zomba, we also estimated an average cluster size of 8000 eligible women per health facility and a coefficient of variation of the cluster sizes of 0.35. Finally, we estimated that our intra-cluster correlation coefficient (ICC) will be between 0.12 and 0.19, based on other similar studies performed in Malawi, where the ICC ranged from 0.004 to 0.20 [25, 26]. With 16 randomized facilities (8 per arm), we initially estimated that we would have at least 80% power to detect a difference of at least 25–30% between our 2 arms, even if the proportion of women screened in the clinic-only arm is as low as 40%. For example, if the clinic-only arm found that 40% of women had been screened, we would have 80% power to detect a difference if the clinic + community arm had screened at least 75% of women in their catchment areas.

However, after performing site selection and randomization, we learned that the two central/district hospitals selected could not be assigned to model 2 as their HSAs did not perform community-based services. Therefore, we dropped these 2 hospitals from our sample size calculations and decreased our average cluster size to 3400 eligible women accordingly. With an ICC of 0.15 and coefficient of variation of cluster sizes of 0.35, we will have at least 83% power to detect of difference of at least 30% between our 2 arms (with 7 facilities in each arm), even if the proportion of women screened in the clinic-only arm is as low as 40%. All power calculations were calculated in R (Version 3.5.1, clusterPower package).

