#### Endline Household Survey

The Endline Household Survey, conducted at months 13–15 after implementation, will be the primary tool to assess the uptake of CCSPT and FP services among women in the catchment areas of the health facilities. Households will be sampled in a two-stage sampling design. Stage 1 will include a random sample of enumeration areas (EAs) from all of the facilities’ catchment areas. This random sample will be selected with the number of EAs proportional to the size of the catchment area. In each selected EA, we will undertake a household listing to create a sampling frame of households for the survey. In stage 2, a random sample of households will be selected. Our target sample size is up to 8000 women aged 15–50 years from the 16 health facility catchment areas. The age range is intended to include women most likely to utilize FP services, as well as those in the target range for CCSPT. With the expectation of ~1.1 women aged 15–50 in our households, the sample will include ~8000 households selected from 266 EAs selected proportionally from facility catchment areas (randomly selecting ~30 households/EA). Parental consent will be obtained for participants 15–17 years old, as described in the “Ethical considerations” section. If a randomly sampled woman does not consent for the survey, she will be replaced with another randomly selected woman from her EA.

Women aged 15–50 years will be eligible to participate in the interviewer-administered survey, provided that they have not had their cervix removed. The survey will cover demographic information, reproductive health information, HIV status, distance to the nearest health facility, prior FP use, FP use during project implementation, prior CCSPT services received, and CCSPT services received during project implementation.

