#### Cost and budget impact

For the CCSPT intervention proposed, we will calculate the incremental cost of the two models (including both costs incurred and averted), the cost per woman screened, and the cost per cervical cancer case averted. We will also estimate the cost per use of CCSPT and FP services. Cost data will be used to conduct a budget impact analysis from the Malawi MoH perspective.

Micro-costing studies will use the time and motion evaluations, routine service utilization data, study budgets, workload assessments, structured observations, and client exit surveys. Estimated costs will also be abstracted from published government reports and the health economics literature, based on methods from published cost-effectiveness research [31, 32]. Costs will be compared between the two models and between each model and the current standard of care (VIA and cryotherapy). The number of women screened will be based on the results of the Endline Household Survey.

To estimate the impact of HPV screening and treatment, we will use a decision analysis model to simulate HPV infection, clearance, persistence, and progression to high-grade cervical intraepithelial lesion and cancer (CIN2+), informed by previous modeling work [33, 34]. Our modeling will also capture differences in cost and outcomes by HIV status.

For budget impact analysis, we will consider direct program costs, to ensure that measurements of MoH costs reflect the opportunity cost of the resources used in delivering services. The primary analysis will be from the programmatic perspective, the point of view of decision makers. A secondary analysis will be presented from the societal perspective, using data on economic productivity for disease averted and costs of accessing services.

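### VIA-only screens can be credited to the HPV models in absolute uptake and in the denominator of cost per woman screened, because neither measure is tied to a screening test

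*Protocol article*

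**What the plan says.** All references are to the protocol article.

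- **Outcome.** The abstract (Methods) states: "Our primary outcome will be the uptake of cervical cancer screening and family planning services during the 18 months of implementation". The Analysis plan (Endline Household Survey) gives the screening outcome as "the proportion of eligible women who have received CCS during the 18 months of study implementation". Neither names a test. The treatment outcome in the same sentence does name a technology: "the proportion of treatment-eligible women who received thermal ablation during the study period".
- **Concomitant care.** The Design section, in the text after Table 2, places no restriction on other care: "Specifically, facilities are permitted to continue offering VIA and cryotherapy". This applies to both models.
- **Survey content.** The survey covers "prior CCSPT services received, and CCSPT services received during project implementation". Whether it records the test used is not stated. The Background section applies the term CCSPT to the existing VIA-based national programme, so the article's own vocabulary includes VIA.
- **Planning assumption.** Sample size calculations link the expected 40–50% uptake to the new test: "We estimated that with the introduction of HPV self-sampling in our clinic-only arm".
- **Cost analysis.** The Analysis plan (Cost and budget impact) sets out a cost per woman screened for the proposed intervention and compares each model with VIA and cryotherapy. It states: "The number of women screened will be based on the results of the Endline Household Survey". A separate paragraph says: "To estimate the impact of HPV screening and treatment, we will use a decision analysis model".

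**The concern.** The stated aim is to compare two ways of delivering self-sampled HPV testing. A woman who had only VIA during the period has received cervical cancer screening, so on the plain reading she is a success for her model. The survey samples residents of the catchment areas, not clinic clients. A VIA screen obtained at a non-study facility can therefore count too; the Setting section reports 130 public facilities providing VIA in 2015.

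Two results are exposed. Each model's absolute uptake may be read as what HPV self-sampling achieved when part of it is background VIA. Cost per woman screened may divide the cost of the HPV programme by a count that includes women who used no HPV cartridge, and the result is then compared with VIA itself. Both figures are meant to inform Ministry of Health decisions.

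**Working it through.** **1. The plan's own figure.** Inputs from Sample size calculations: 7 facilities per arm (k), average cluster size m = 3400, ICC 0.15, coefficient of variation 0.35, 40% against 70%. Two-sided alpha of 0.05 is assumed, as none is stated.

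- Design effect = 1 + ((0.35² + 1) × 3400 − 1) × 0.15 = 573.3
- SE = √[(0.40×0.60 + 0.70×0.30) × 573.3 / (7 × 3400)] = 0.104
- Power = Φ(0.30/0.104 − 1.96) = 82.2%

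This is within one point of the stated 83%. Power is not the issue here; the calculation only anchors the 40% and 70% used below.

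**2. Effect on the randomised difference.** The VIA rate v is an assumption throughout.

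*Scenario A: HPV uptake is 40% and 70%, and VIA reaches a share v of the women not HPV-screened.* Model 1 total = 40 + 60v; model 2 total = 70 + 30v.

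| v | Model 1 | Model 2 | Difference | Power | VIA share of screens, model 1 / model 2 |
|---|---|---|---|---|---|
| 5% | 43.0% | 71.5% | 28.5 points | 78% | 7.0% / 2.1% |
| 10% | 46.0% | 73.0% | 27.0 points | 74% | 13.0% / 4.1% |
| 20% | 52.0% | 76.0% | 24.0 points | 65% | 23.1% / 7.9% |

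*Scenario B: totals are 40% and 70%, with an equal number of VIA-only points inside each.* The difference is 30 points in total uptake and 30 points in HPV-based uptake.

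In A the difference shrinks; in B it is unchanged. Neither scenario inflates model 2 against model 1.

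**3. Effect on cost per woman screened (Scenario B).** Suppose the numerator holds only HPV programme costs and the denominator holds all screens. Cost per HPV-screened woman is then understated by the proportion (VIA-only points)/(total points):

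- 5 points: 5/40 = 12.5% in model 1; 5/70 = 7.1% in model 2
- 10 points: 10/40 = 25.0% in model 1; 10/70 = 14.3% in model 2

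The cost ratio between models shifts by (40/35)/(70/65) = 1.061 at 5 points and (40/30)/(70/60) = 1.143 at 10 points, towards model 1. Scenario A points the same way: (43/40)/(71.5/70) = 1.05 at v = 5% and (46/40)/(73/70) = 1.10 at v = 10%. If VIA were the same *share* of screens in each arm (say 4 of 40 and 7 of 70), the ratio would not move.

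**4. A lower illustration.** The only VIA figure given is 26.5% ever screened by 2015, under a programme begun in 2004. Spread evenly over those 11 years, this is 26.5/11 × 1.5 = 3.6 points per 18 months, counting first screens only. The understatement is then 3.6/40 = 9.0% and 3.6/70 = 5.1%, and the ratio shift is (40/36.4)/(70/66.4) = 1.04.

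**The case against.** Any-test uptake is a proper pragmatic outcome. The hypothesis in Aims and objectives concerns screening as such, and the benchmarks in Sample size calculations (26.5% and the 80% national target) are all-screening figures. An HPV-only outcome would count replacement of VIA by HPV testing as a gain. This stands, and the primary outcome should not change.

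The survey form may already record the test, since an article need not list survey items. This also stands. It does not settle which screens enter the reported uptake or the cost denominator.

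HPV test volumes are collected separately. Facility preparation describes new registers for HPV laboratory testing and community screening, and the cost section lists routine service data among its sources. However, that section names the survey as the source of the number screened, so the registers can only cross-check it.

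VIA provider time may be included in the costs. If so, numerator and denominator match better, and the understatement shown above does not apply in full. The result would then be a blend of HPV and VIA screening rather than the cost of the HPV models.

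Eligible women who come to the CCSPT clinic are offered self-collection, so VIA-only screening may be uncommon. This is possible; the documents give no rate either way.

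**Conclusion.** The point holds for absolute uptake and for the denominator of cost per woman screened. VIA is permitted in both arms, the outcome names no test, and the cost count comes from the same survey. The size is unknown. The 12.5–25% and 7–14% understatements rest on an assumed 5 to 10 VIA-only points, totals of 40% and 70%, and a numerator limited to HPV programme costs; at 3.6 points they fall to about 9% and 5%.

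A reader might infer four stronger things that the documents do not support:

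- *That the plan rules VIA-only screens to be CCS.* No sentence says so and none excludes them; it follows from an outcome with no test named.
- *That the randomised comparison is biased towards model 2.* Background VIA common to both arms leaves the difference unchanged or dilutes it.
- *That cases averted are overstated.* The sentence on the survey count closes the costing paragraph. The decision model is described separately, for HPV screening, and its uptake input is not specified. Carry-over is a risk, not a stated rule.
- *That the cost comparison is tilted towards model 1.* This depends on how VIA splits between the arms, which is assumed.

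The change is worth making because test type is hard to recover once the survey has closed.

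**What to change.** Leave the primary outcome and the care offered at sites as they are.

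- **Analysis plan, Endline Household Survey.** State that CCS means any screening test. Classify each reported screen by test (HPV self-sample, or VIA without an HPV test) and by place (study facility, community clinic, non-study site). The VIA category must exclude women who had an HPV test, because HPV-positive women also receive VIA under the algorithm. Report HPV-based uptake by model beside any-CCS uptake.
- **Analysis plan, Cost and budget impact.** Use HPV-screened women as the denominator for the HPV models' cost per woman screened, cross-checked against the HPV laboratory registers. Wherever VIA-only screens enter the cost analysis or the decision model, give them VIA cost and VIA test performance.

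The cost is at most two survey response items, if they are not already on the form, plus analysis wording. Recall of test type may be imperfect, and HPV-based uptake will be somewhat lower than total uptake.

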Introducing a screen-and-treat strategy that combines these innovations—self-sampling, rapid HPV assays, and thermal ablation—promises to improve screening and treatment rates in resource-limited settings including Malawi. However, success requires considering key implementation questions around how to target healthy women and how to reach rural women who have poor access to health facilities. Integrating cervical cancer screening with family planning (FP) services is a promising strategy because many women who access FP services are in the appropriate screening age range and sexually-active. Existing structures to deliver community-based FP services can be utilized to reach women in rural and isolated areas. Any solution for increasing CCSPT services in sub-Saharan Africa must be applicable to rural populations, since an estimated 60–75% of women who develop cervical cancer in sub-Saharan Africa live in rural areas [14].

In many countries, community health workers provide a vital link between health facilities and rural populations. Community-based FP services have been effective in increasing FP uptake in many countries [15], including in Malawi where 80% of the population is rural [16, 17]. Community health workers in Malawi, known as health surveillance assistants (HSAs), provide FP services to rural women through outreach and village clinics. Experience from other countries suggests that community health workers like HSAs can be successfully trained to offer self-sampling for HPV screening in rural areas [18, 19]. However, providing community-based screening introduces additional challenges for follow-up given that same-day screening and treatment will not be conducted. Understanding the impact of community-based screening on loss to follow-up is important given that one of the primary shortcomings in Malawi’s CCSPT program has been the low rate of treatment among screen-positive women. Thermal ablation may be more scalable than cryoablation but would only improve access if women are successfully informed of their results and linked to care at facilities.

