### Description of models

In both model 1 and model 2, through group educational talks and one-on-one counseling, women will be educated about cervical cancer screening and the opportunity to perform self-sampling for HPV testing. The facility staff will be encouraged to hold the CCSPT educational talks in waiting rooms for the FP clinic, antiretroviral therapy (ART) clinic, and other clinics.

Once a woman presents to the CCSPT clinic at the facility, she will be offered self-collection if she meets the following eligibility criteria: (1) aged 25–49 years old, (2) no history of total hysterectomy, (3) no history of cervical cancer, and (4) not currently pregnant. Self-collected samples will then be sent to the facility laboratory for high-risk HPV (hrHPV) testing using the GeneXpert® (Cepheid Inc, Sunnyvale, CA, USA) platform. We chose to use the Xpert HPV assay because it offers several advantages over other commercially available HPV assays: results are available within 1–2 h, all reagents are contained in one cartridge, and laboratory personnel only need a short training course to use the machines. In addition, the Xpert HPV assay has been validated in Malawi, and many facilities in Malawi have already invested in Xpert machines for tuberculosis diagnostic testing [27].

Women who screen positive for hrHPV at the clinic will be offered same-day VIA to determine whether they are eligible for ablative treatment. Eligibility for thermal ablation requires that (1) no cervical lesions or any visible lesion covers <75% of the cervix and can be seen in its entirety, (2) the lesion does not extend into the endocervical canal or to the vaginal wall, (3) the squamocolumnar junction is visible, (4) the client is more than 3 months postpartum if recently pregnant, (5) there is no suspicion of cervical cancer, (6) there are no polyps or scarring impeding contact of the probe, and (7) there is no evidence of current menstruation or cervicitis. HPV-positive and treatment-eligible women will be offered thermal ablation on the same day of screening.

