In model 2, women living in the health facility’s catchment area will also be offered self-sampling in the community. HSAs and other health facility staff will give educational talks about self-sampling to groups of women at village and outreach clinics. Interested women can perform self-sampling on the day of the community clinic, and HSAs will transport the sample back to the health facility for testing. Women can receive results at the next community clinic or by presenting to the associated health facility. If any women screens HPV-positive, she will be referred for VIA and possible treatment. Patient flow is illustrated in Fig. 2, with light blue shading for the community-based components.

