Studies in other low-resource countries have demonstrated that training community health workers like HSAs to offer self-sampling is feasible and has the potential to improve screening coverage. In addition, the WHO now recommends self-testing options for sexual and reproductive health, including HPV self-sampling for primary cervical cancer screening [4]. A cluster randomized study in Argentina demonstrated a four-fold increase in screening rates with community health workers offering HPV self-sampling, compared with community health workers counseling women to undergo clinician-sampling at a facility [18]. In Uganda, screening was higher with community-based HPV self-sampling compared to the control of clinic-based VIA screening, in preliminary results from a cluster randomized trial [19]. The same project showed that community-based HPV self-sampling was more cost-effective than clinic-based VIA screening, with a wide margin for increasing costs of the HPV-based program [35]. Our study will investigate the feasibility of community self-sampling in Malawi and provide a direct comparison to facility-only services. Using stratified randomization further allows us to assess implementation success in a variety of settings, including urban and rural, district-level and local, and public and private facilities.

Linking community-screened women with appropriate care is crucial for cervical cancer prevention and can be especially challenging with community-based screening. In the pilot results of a Uganda trial comparing community HPV screening versus clinic-based VIA screening, over 50% of 73 women who were positive for hrHPV after community self-sampling could not be reached by telephone for result delivery [19]. Loss to follow-up is already a concern with the current standard of care in Malawi: only 43% of women who are VIA-positive receive appropriate treatment [3]. Our study will provide insight into whether appropriate follow-up is feasible with community-based screening.

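### Key outcome (2), ablation among treatment-eligible women, is conditional on having had VIA, so it cannot show HPV-positive women lost before VIA, the loss expected mainly in model 2

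*Protocol article*

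**What the plan says.** In the protocol article, Analysis plan, Endline Household Survey, the second of three key outcomes is "the proportion of treatment-eligible women who received thermal ablation during the study period". That section does not define treatment-eligible. The only meaning given elsewhere is a finding at examination. The abstract's Methods describe "visual inspection with acetic acid for HPV-positive women to determine ablative treatment eligibility", and Description of models says that women positive at the clinic are "offered same-day VIA to determine whether they are eligible for ablative treatment". Some of the listed criteria can be judged only by looking at the cervix, for example that "the squamocolumnar junction is visible".

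The route to VIA differs by place of screening. At facilities it is offered the same day. For community screening, offered only in model 2, the sample travels to the facility and results come back at a later community clinic or on a visit to the facility. Then: "If any women screens HPV-positive, she will be referred for VIA and possible treatment". The note to Fig. 2 confirms that results for these women are delayed.

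The Background states: "Understanding the impact of community-based screening on loss to follow-up is important". The Discussion promises: "Our study will provide insight into whether appropriate follow-up is feasible with community-based screening".

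**The concern.** A denominator of treatment-eligible women contains only women who completed the step from positive test to VIA. That step happens after randomisation, and it is organised differently in the two models. A community-screened woman who never receives her result, or receives it and does not attend, has no eligibility status and is not counted. She can still count as screened in key outcome (1). The survey cannot easily recover her either, since a woman who was never told her result cannot report that it was positive.

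The other two key survey outcomes are screening uptake and modern contraceptive use, so none of the three has HPV-positive women as its denominator. The Design section gives the survey the task of comparing treatment rates between the models. A reader of the results could see equal treatment completion and conclude that linkage to care works as well in model 2, although the outcome was never able to show otherwise.

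The benchmark in the Background and Discussion, 43% receiving appropriate treatment, is per screen-positive woman. An outcome per treatment-eligible woman cannot be set against it.

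**Working it through.** The article states no figure for the treatment outcome, so there is none to reproduce. Its 83% power statement concerns screening uptake only and is not at issue here.

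**Structure.** For HPV-positive women let V be the proportion who have VIA, E the proportion of those found eligible, and T the proportion of eligible women who are ablated.

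- Stated outcome: T.
- Ablated per HPV-positive woman: V × E × T.

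V does not appear in the stated outcome, so whatever happens before VIA leaves it unchanged.

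Model 2 screens by both routes. If a share s of its positives is community-screened, with VIA attendance Vc, and the rest are facility-screened, with attendance Vf, then V in model 2 is (1 − s)Vf + sVc. With E and T equal across models, and Vf equal at facilities in both, the difference per HPV-positive woman (model 1 minus model 2) is E × T × s × (Vf − Vc). It is positive whenever fewer community-screened than facility-screened positives reach VIA.

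**Inputs.** The article gives none of V, E, T or s, so all are assumptions. The nearest figure is in the Discussion: in a Ugandan pilot, more than half of 73 hrHPV-positive women could not be contacted by telephone with their result. That loss comes before VIA, but the setting and the way results are returned differ from this trial.

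**Set A:** E = 0.90, T = 0.90, Vf = 0.95.

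- Stated outcome: 90% in both models, difference 0.
- Model 1 per HPV-positive woman: 0.95 × 0.90 × 0.90 = 77%.
- Model 2 with s = 0.50 and Vc = 0.50: V = 0.50 × 0.95 + 0.50 × 0.50 = 0.725, and 0.725 × 0.81 = 59%. Difference 18 points.
- Smallest gap tried, s = 0.25 and Vc = 0.70: 0.81 × 0.25 × 0.25 = 5 points (model 2 at 72%).
- Largest gap tried, s = 0.75 and Vc = 0.30: 0.81 × 0.75 × 0.65 = 39.5, about 40 points (model 2 at 37%).

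**Set B:** E = 0.80, T = 0.95, Vf = 0.95, Vc = 0.50.

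- Stated outcome: 95% in both models, difference 0.
- Facility-screened: 0.95 × 0.80 × 0.95 = 72.2%. Community-screened: 0.50 × 0.80 × 0.95 = 38.0%.
- Model 2 with s = 0.50: (72.2 + 38.0) / 2 = 55.1%. Difference from model 1: 72.2 − 55.1 = 17 points.

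**Allowing for screening.** Take the 40% v 70% screening scenario in Sample size calculations, equal HPV prevalence and set B. Ablated per HPV-positive woman in the catchment, screened or not, is 0.40 × 0.722 = 29% in model 1 and 0.70 × 0.551 = 39% in model 2.

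**The case against.** **The outcome is not primary.** This stands. The abstract names uptake of screening and family planning as primary. Both hypotheses under objective 1 concern uptake, and the sample size rests on screening. Loss to follow-up is discussed in the Background and Discussion but is not among the numbered objectives. The trial's main comparison is untouched.

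**The data exist.** Table 2 lists monthly clinic, HSA and lab register data, and Facility preparation adds new registers for HPV testing and community screening. So the loss need not stay hidden. But the registers are listed under the cost objective, and no comparison between models of VIA attendance, or of treatment among HPV-positive women, is stated.

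**Detail may sit in the full protocol or SAP.** That would excuse an omission. Here the article states a denominator. If all HPV-positive women were meant, the wording conflicts with the article's own account of eligibility and still needs correcting.

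**HPV-positive women are also a post-randomisation group.** This is correct. A woman must be screened to be known as positive, and screening is what the models are meant to change. The wider denominator moves the conditioning one step earlier and does not remove it.

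**Counting thermal ablation only is defensible,** since it is the trial's intervention. But the Design section lets facilities continue cryotherapy, and no difference in its use between models is shown in either direction. Counting both is a precaution.

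A reader might also draw three stronger conclusions that the article does not support:

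- That the models differ by 34 points (72% v 38% in set B). Those figures compare facility-screened with community-screened women. Model 2 offers both routes.
- That model 2 would treat far fewer women with HPV. Under the assumed rates this holds only among women already screened. With the article's own screening scenario the catchment figures are 29% v 39%, so model 2 treats more.
- That the outcome is shown to favour model 2. The direction is an inference from delayed results and referral. Women in model 1 can also leave before VIA.

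**Conclusion.** The concern holds as a defect in the definition of one key, non-primary outcome. As worded, it measures completion of the last step among women who reached that step. It cannot show whether HPV-positive women were informed and linked to care, which is the question the Background and Discussion raise about community screening.

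The size cannot be known from the article. With half of model 2's positives community-screened and half of those reaching VIA, the hidden gap is 17 to 18 points per HPV-positive woman. It runs from about 5 to 40 points for a community share of 25% to 75% and VIA attendance of 30% to 70%. The stated outcome shows 0 throughout. These figures assume equal eligibility and equal ablation among eligible women in both models, and 95% VIA attendance after facility screening.

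The 43% benchmark is not comparable with the stated outcome. A figure per HPV-positive woman comes closer, but the Discussion describes the benchmark group as VIA-positive, so the match would not be exact.

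**What to change.** 1. From the lab, HSA and clinic registers, report by facility, model and place of screening, among all HPV-positive women: (a) the proportion who had VIA; (b) the proportion who completed VIA and, if eligible, received ablative treatment, counting thermal ablation and any cryotherapy.
2. Keep ablation among treatment-eligible women as a conditional process measure, define treatment-eligible where it is used, and label it as applying only to women who had VIA.
3. In any survey version with all screening-eligible women as denominator, count women who were screened but received no result as not completed.
4. State that the HPV-positive denominator is itself conditional on being screened, and present it beside screening uptake.

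**Cost.** No new data collection, since the registers are already collected monthly. The new measures do rest on a different source from the catchment survey. The registers are de-identified, so the measures are facility-level ratios of counts. They may include women from outside the catchment area and may not link a community test to a later VIA. These limits should be stated with the results.
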